### Sample Size Estimation

The sample size calculation for this trial is based on the data from HBPT plus pharmacist management trial on the hypertension population.^
22
^ Adequate power will be used to detect a clinically important absolute difference in mean SBP of 10 mmHg between the intervention arm and the control arm (usual care). Using a 2-sample t-test, alpha of 0.05 and power of 0.80, and assuming a common standard deviation of 19 mmHg, the required sample size will be ~58 patients per arm, or 116 in total. Accounting for ~20% attrition over 1 year, we will recruit 73 patients per arm, for a total of 146 patients. This sample size is also powered to detect a difference of 20% in the proportion of patients who maintain the guideline target of SBP (alpha 0.05, power 80%, and assuming event occurs 50% in the control group).^
22
^

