**Measurements::**

Eligible patients will be randomized 1:1 to HBPT + BP case management versus HBPT + usual care. In the intervention arm, BP will be measured 4 times daily for 1 week, with medications titrated up or down by the study case manager until guideline targets (systolic BP [SBP]: <130 mmHg) are achieved. Once BP is controlled, (ie, to guideline-concordant targets), this 1-week protocol will be repeated every 3 months for 1 year. Patients in the control arm will also follow the same BP measurement protocol; however, there will be no interactions with the case manager; they will share their BP readings with their primary care physicians or nurse practitioners at scheduled visits.

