### Plan for Data and Statistical Analysis

Baseline statistics and the outcome variables will be described using counts and proportions, mean (SD) or median (interquartile range) as appropriate. All analyses will follow the intention-to-treat principle. We will estimate the effect size as the mean difference of SBP between groups at 12 months using a mixed linear-regression model include fixed-effects term for time point (6 months and 12 months), intervention, their interaction, and a random-effect term for participants. For the dichotomous outcomes (patients who maintained the SBP guideline and adverse outcomes), we will use Poisson regression with robust error variance to test the effect of the intervention.^
50
^ Continuous outcomes without repeated measurement will be examined using linear regression. We will adjust for eGFR for all the analyses. All estimated effect sizes will be reported along with 95% confidence intervals, and P<0.05 was considered statistically significant. We will analyze the data using Stata/MP 17.0 software (www.stata.com).

We will use multiple imputation method for missing data. Imputation of missing SBP values will only apply in instances when participants do not have any blood pressure recordings for the entire week. We will impute the missing SBP within each randomized group using age and sex separately at 6 months and 12 months. Estimate from each imputed data set will be combined using Rubin’s method.^
51
^ No interim analyses are planned due to the short duration of the study. However, for subgroup analysis, we will use the model from the analysis for primary analysis to explore the relationship between intervention and eGFR groups, age groups, the presence of diabetes, and so on.

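### The planned sample does not have 80% power for a 20-point difference in the proportion at SBP target: power is about 60% after the planned attrition and about 70% with none.

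*Protocol article*

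**What the plan says.** All the relevant text is in the protocol article, Methods, Sample Size Estimation.

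- **Primary calculation.** The target is a "clinically important absolute difference in mean SBP of 10 mmHg". The method is given as: "Using a 2-sample t-test, alpha of 0.05 and power of 0.80, and assuming a common standard deviation of 19 mmHg". The result is that "the required sample size will be ~58 patients per arm, or 116 in total".
- **Attrition.** "Accounting for ~20% attrition over 1 year, we will recruit 73 patients per arm, for a total of 146 patients".
- **Secondary claim.** "This sample size is also powered to detect a difference of 20% in the proportion of patients who maintain the guideline target of SBP". The parenthesis that follows gives the assumptions: "alpha 0.05, power 80%, and assuming event occurs 50% in the control group".

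The section Plan for Data and Statistical Analysis says the dichotomous outcomes will be analysed by Poisson regression with robust error variance, which tests a risk ratio. It sets the reporting convention: "All estimated effect sizes will be reported along with 95% confidence intervals, and P<0.05 was considered statistically significant".

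**The concern.** A sample that just reaches 80% power for a standardised mean difference of 10/19 = 0.53 is unlikely to reach 80% power for 50% versus 70%. A binary outcome with a control rate near one half carries less information per patient, and the 20-point effect corresponds to a standardised difference of only about 0.4 (0.20 divided by a standard deviation near 0.49). The claim gives all its inputs, so it can be tested directly.

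Target attainment underlies two of the five listed secondary outcomes (at target at the end of the study, and at target throughout), and it is the only secondary endpoint for which the article claims power. If true power is well below 80%, a non-significant result would be read as evidence that case management does not improve control, when the trial had a large chance of missing the effect it said it could detect.

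**Working it through.** **Inputs.** Sample Size Estimation gives alpha 0.05, power 0.80, control proportion 0.50, a difference of 20% (read as 20 percentage points), 58 analysable per arm, 20% attrition and 73 recruited per arm. Allocation is 1:1. The section does not say whether tests are one- or two-sided; step 1 settles this.

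**Step 1. Reproduce the primary figure.**
- Normal approximation: n = 2 × (1.960 + 0.842)² × (19/10)² = 56.7 per arm.
- Solving with the t distribution gives 57.6, so 58 per arm, with power 80.2%.
- Attrition: 58/0.80 = 72.5, so 73.

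The stated 58 and 73 are therefore correct with a two-sided test. A one-sided t-test at 0.05 would have needed 45.3, so 46 per arm. The section is thus working with a two-sided alpha of 0.05, in line with the 95% intervals and P<0.05 in the analysis section.

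**Step 2. Required size for the binary outcome.** Take p₁ = 0.50, p₂ = 0.70 and mean p̄ = 0.60.

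n = [z(α/2)·√(2p̄(1−p̄)) + z(β)·√(p₁(1−p₁) + p₂(1−p₂))]² / (p₂ − p₁)²

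- √(2 × 0.60 × 0.40) = 0.6928
- √(0.25 + 0.21) = 0.6782
- n = [(1.960 × 0.6928 + 0.8416 × 0.6782) / 0.20]² = [(1.3579 + 0.5708) / 0.20]² = 93.0 per arm
- With continuity correction: 102.8, so 103 per arm
- Allowing for 20% attrition: 93/0.80 = 116.25, so 117 recruited per arm (234 in total), against 73 (146) planned

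**Step 3. Power at the planned size.** Power = Φ{[0.20·√n − 1.3579] / 0.6782}.

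- n = 58: (1.5232 − 1.3579)/0.6782 = 0.244, power **59.6%**
- n = 73: (1.7088 − 1.3579)/0.6782 = 0.517, power **69.8%**

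By symmetry, 50% versus 30% gives the same values.

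**Step 4. Other methods, two-sided 0.05, 50% versus 70%.**

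| Method | 58 per arm | 73 per arm |
|---|---|---|
| Pooled variance | 59.6% | 69.8% |
| Unpooled variance | 61.2% | 71.2% |
| Arcsine | 60.1% | 70.1% |
| Chi-square, exact enumeration | 59.2% | 70.6% |
| Fisher's exact | 51.9% | 64.5% |
| Wald test of log risk ratio | 57.3% | 67.2% |

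The last row is the closest to the planned robust Poisson model: log(0.70/0.50) = 0.3365, with standard error √(0.5/(58 × 0.5) + 0.3/(58 × 0.7)) = 0.1569 at 58 per arm, so Φ(0.3365/0.1569 − 1.960) = 57.3%.

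**Step 5. Detectable difference.** From a control rate of 50%, 80% power is reached at about 25.0 points with 58 per arm and about 22.5 points with 73.

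**Step 6. Other readings.**
- *One-sided 0.05:* 71.4% at 58 per arm and 79.9% at 73.
- *20% as a relative increase (50% to 60%):* 18.9% at 58 and 22.7% at 73.
- *Another control rate:* on a grid in 5-point steps, a 20-point increase has less than 80% power at 58 per arm for every control rate from 10% to 70%.

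**The case against.** **One set of choices gives the stated figure.** A one-sided test at 0.05 with all 73 recruited patients per arm analysed has 79.9% power. This may be how the sentence arose, though the article does not say. It does not rescue the claim. It changes sidedness within a section whose primary figure reproduces only two-sided, and it treats as fully observed the patients who were added to cover attrition. One-sided power with the 58 who remain is 71.4%.

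**Multiple imputation keeps all randomised patients in the analysis.** The plan imputes missing SBP within arm from age and sex. That would not be expected to recover the lost information, and full information on 73 per arm still gives only about 70%.

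**Adjustment for eGFR may alter power.** It may, but the article gives no figure for this and the stated 80% does not rely on it.

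**The outcome is secondary and the correction changes no number of patients.** This stands. The primary calculation is sound, and no analysis or decision rule depends on the sentence. Reporting 95% confidence intervals will also show the actual precision, which limits the risk of misreading. It does not make the stated power correct.

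Two qualifications also stand. Two-sidedness is inferred, not stated. And the 70% without attrition is approximate, since the other two-sided methods give 64.5% to 71.2%.

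**Conclusion.** The power statement is wrong under the article's own assumptions. For 50% versus 70% at two-sided 0.05, the trial has about 60% power with the 58 per arm expected to be analysable and about 70% with no attrition, against the 80% stated. The chance of missing a true 20-point difference is about 40% instead of 20%. Supporting the claim would take 93 analysed per arm, 1.6 times the 58 planned.

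This rests on reading the difference as absolute, on a two-sided test and on unadjusted comparisons. The first is the natural and more favourable reading; the second is what reproduces the 58 per arm. No two-sided method tried exceeds about 71%, even with complete follow-up.

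How the error arose cannot be established. The required recruitment of about 116 to 117 per arm lies close to the trial's analysable total of 116, so a per-arm figure may have been taken for a total; the one-sided route is at least as plausible. The conclusion depends on neither.

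**What to change.** Replace the last sentence of Sample Size Estimation with wording such as:

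> With 58 analysable patients per arm the trial has about 60% power (about 70% with 73 per arm) to detect 50% versus 70% of patients at SBP target, two-sided alpha 0.05. The difference detectable with 80% power is about 25 percentage points.

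State that alpha is two-sided, and say which of the two target outcomes is meant (at target at the end of the study, or throughout). It would also help to describe the outcome as supportive, so that a non-significant result is read through its confidence interval. Deleting the power claim altogether is an acceptable alternative.

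The cost is one sentence and a less favourable stated power. Enrolment, the primary analysis and trial conduct need not change. Keeping the 80% claim for 20 points would instead require about 117 recruited per arm (234 in total), which a secondary outcome does not justify.

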### Plan for Data and Statistical Analysis

Baseline statistics and the outcome variables will be described using counts and proportions, mean (SD) or median (interquartile range) as appropriate. All analyses will follow the intention-to-treat principle. We will estimate the effect size as the mean difference of SBP between groups at 12 months using a mixed linear-regression model include fixed-effects term for time point (6 months and 12 months), intervention, their interaction, and a random-effect term for participants. For the dichotomous outcomes (patients who maintained the SBP guideline and adverse outcomes), we will use Poisson regression with robust error variance to test the effect of the intervention.^
50
^ Continuous outcomes without repeated measurement will be examined using linear regression. We will adjust for eGFR for all the analyses. All estimated effect sizes will be reported along with 95% confidence intervals, and P<0.05 was considered statistically significant. We will analyze the data using Stata/MP 17.0 software (www.stata.com).

We will use multiple imputation method for missing data. Imputation of missing SBP values will only apply in instances when participants do not have any blood pressure recordings for the entire week. We will impute the missing SBP within each randomized group using age and sex separately at 6 months and 12 months. Estimate from each imputed data set will be combined using Rubin’s method.^
51
^ No interim analyses are planned due to the short duration of the study. However, for subgroup analysis, we will use the model from the analysis for primary analysis to explore the relationship between intervention and eGFR groups, age groups, the presence of diabetes, and so on.

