### Design, Randomization, and Allocation

We have designed this study as a 2-arm pragmatic RCT comparing the clinical care of remote dwelling hypertensive CKD patients. We will randomly assign the patients with CKD and hypertension to each study arm (1:1) that is, HBPT plus protocol-based case management versus HBPT plus usual care (Figure 2). A randomized permuted block design of 4 and 6 will be used. The random allocation sequence will be computer generated using STATA 17 software (StataCorp. 2021. Stata Statistical Software: Release 17. College Station, Texas: StataCorp LLC) and allocation will be concealed by web-based central randomization using The Research Electronic Data Capture System (REDCap version 8.8.2; 2018 Vanderbilt University). Participants and clinicians will not be blinded to group assignment.

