### Outcomes

The primary outcome will be the mean difference (MD) in home SBP at 12 months, from baseline values. Secondary outcomes will include (1) proportion of patients with SBP within guideline target at end of the study, from baseline; (2) Proportion of patients who remained within target SBP throughout the study; (3) user acceptability of HBPT for BP control; (4) cost-effectiveness and cost utility of HBPT combined with a protocol-based case management approach, and (5) adverse events reported.

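### The primary mixed model has no baseline SBP term, so it gives up free precision on an outcome defined from baseline; validity and planned power are unaffected

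*Protocol article*

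**What the plan says.** The Outcomes section states: "The primary outcome will be the mean difference (MD) in home SBP at 12 months, from baseline values". The Abstract and the Study Objectives describe the aim in the same way.

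The Plan for Data and Statistical Analysis then states: "We will estimate the effect size as the mean difference of SBP between groups at 12 months". The model is "a mixed linear-regression model include fixed-effects term for time point (6 months and 12 months), intervention, their interaction, and a random-effect term for participants". The one covariate is given by "We will adjust for eGFR for all the analyses".

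Two other places bear on whether baseline SBP enters by another route. In Design, Randomization, and Allocation: "A randomized permuted block design of 4 and 6 will be used"; no stratification factor is named. In the missing-data paragraph: "We will impute the missing SBP within each randomized group using age and sex separately at 6 months and 12 months"; baseline SBP is not among the predictors.

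The Sample Size Estimation section powers the trial for a "clinically important absolute difference in mean SBP of 10 mmHg between the intervention arm and the control arm", using a two-sample t-test with alpha 0.05, power 0.80 and a common SD of 19 mmHg. This gives 58 per arm, raised to 73 per arm for about 20% attrition.

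**The concern.** The outcome is worded relative to baseline, yet baseline SBP has no place in the model that analyses it. This is more than a detail left to an analysis plan: the article lists the time levels, the fixed effects, the random effect and the covariate. An analysis plan that followed that list would have no baseline SBP term.

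The participant random effect does not fill the gap, because it is estimated from post-randomisation values only. Eligibility does not fill it either. Treated hypertension is enough to enter, no SBP threshold is set, and only hypertensive urgency or emergency is excluded. Patients with controlled and uncontrolled pressure can therefore both be randomised, and baseline SBP may vary considerably.

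At stake is the width of the primary confidence interval, and how far the result of this one trial can be moved by a chance difference between arms at entry.

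**Working it through.** **Inputs from the protocol article:** difference 10 mmHg, SD 19 mmHg, alpha 0.05 (taken as two-sided), power 0.80, 58 completers per arm, about 20% attrition.

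**Assumed, not in the document:** the correlation r between baseline and 12-month home SBP, taken as 0.3, 0.5 and 0.7; a baseline SD also equal to 19 mmHg.

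**1. The plan's own figure.** Normal approximation: n = 2 × (1.96 + 0.8416)² × 19² / 10² = 56.7, so 57 per arm. The t-test gives 57.6, so 58 per arm. Attrition: 58 / 0.80 = 72.5, so 73 per arm and 146 in total. The stated figures reproduce. Power at 58 per arm is 0.802 (t) or 0.809 (normal). The calculation uses no baseline information, so it does not depend on adjustment.

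**2. Effect of each choice of response.** With SD 19 at each visit:
- 12-month SBP adjusted for baseline: SD = 19 × √(1 − r²)
- unadjusted change score: SD = 19 × √(2(1 − r))

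Power for 10 mmHg with 58 per arm is shown as t / normal approximation:

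| r | 12-month SBP, unadjusted | Adjusted SD | Adjusted power | Change-score SD | Change-score power |
|---|---|---|---|---|---|
| 0.3 | 0.80 / 0.81 | 18.12 | 0.84 / 0.84 | 22.48 | 0.66 / 0.67 |
| 0.5 | 0.80 / 0.81 | 16.45 | 0.90 / 0.91 | 19.00 | 0.80 / 0.81 |
| 0.7 | 0.80 / 0.81 | 13.57 | 0.98 / 0.98 | 14.72 | 0.95 / 0.955 |

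The 95% CI half-width, 1.96 × SD × √(2/58), is 6.9 mmHg unadjusted. Adjusted, it is 6.6, 6.0 and 4.9 mmHg at r = 0.3, 0.5 and 0.7.

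**3. Simulation of the mixed model.** Settings: 6- and 12-month values, random intercept, equal correlation between all visits, 58 per arm, 300 runs per r. Power without and with baseline SBP was 0.82 and 0.85 (r = 0.3), 0.82 and 0.90 (r = 0.5), and 0.79 and 0.97 (r = 0.7). The Monte Carlo standard error near 0.80 is √(0.8 × 0.2 / 300) = 0.023. Mean estimates were close to −10 mmHg in both models, so neither is biased.

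**4. Chance imbalance.** The baseline difference between arms has standard error 19 × √(2/58) = 3.53 mmHg. An imbalance of one standard error shifts the unadjusted 12-month estimate by r × 3.53 = 1.1, 1.8 and 2.5 mmHg at r = 0.3, 0.5 and 0.7.

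This is not a loss on top of step 2. At r = 0.5 the unadjusted variance 3.53² = 12.4 splits into (0.5 × 3.53)² = 3.1 from baseline imbalance and 3.53² × (1 − 0.25) = 9.3 that remains after adjustment. Lost power and exposure to imbalance describe the same 3.1.

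**5. If 19 mmHg is the SD of change.** The article does not say whether 19 is the SD of the level or of the change. If it is the change, the unadjusted change score has power 0.80. The adjusted SD is then 19 × √((1 + r)/2) = 15.32, 16.45 and 17.52, with power about 0.94, 0.90 and 0.86. Adjustment still gains at every r.

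**The case against.** The other side has a strong case, and most of it stands.

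- **Target of estimation.** A reader might infer that the model fails to estimate the stated outcome. The document does not support that. Under 1:1 randomisation the expected baseline means are equal, so the arm difference in 12-month SBP and the arm difference in change have the same expectation. The sample size section also frames the target as a difference in mean SBP between arms.
- **Power.** A reader might infer that the trial is underpowered. With 12-month SBP as the response and SD 19, it is not: the calculation assumes an unadjusted test. The omission forgoes a gain and does not create a deficit.
- **Imbalance.** Chance imbalance is already inside the unadjusted standard error and confidence interval. It is not systematic bias, and step 4 shows that it must not be counted a second time.
- **Unknown r.** The size of the gain rests on an assumption. Titrating the intervention arm to a common target could weaken the correlation there, and at r = 0.3 the gain is only about 4 percentage points of power.
- **Change-score reading.** The Outcomes wording and a model with only post-baseline times would also fit a change score. The effect-size sentence in the analysis section reads as SBP, not change, but the ambiguity is real. Under either reading the adjusted model is the more precise.

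Two further inferences are tempting and unsupported. One is that follow-up eGFR will be used as the covariate. Nothing says so: eGFR groups are listed as subgroups beside age and diabetes, and the choice of visit is a detail commonly left to the analysis plan. The other is that the Poisson models for target attainment are wrong without baseline SBP. Adding it there would be a refinement; no error has been shown.

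What survives is that a fully listed primary model leaves out a covariate tied to the outcome's own definition, and that including it costs nothing.

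**Conclusion.** The point holds as a free improvement in precision, together with a wording mismatch between the Outcomes and analysis sections. It is not a flaw in validity or in the sample size.

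With 12-month SBP as the response, the gain in power for 10 mmHg with 58 per arm is about 4, 10 and 17 percentage points at r = 0.3, 0.5 and 0.7. Below r of about 0.3 it is small. These figures assume SD 19 mmHg at both visits, 58 completers per arm and the stated range of r, which the document does not supply. Under the change-score reading the gain is about 18, 10 and 2 points (t-test), so it is then largest where r is low.

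**What to change.** In the Plan for Data and Statistical Analysis, do one of the following:
- add baseline mean home SBP, with its interaction with time, as a fixed covariate in the primary mixed model; or
- include baseline as a response time point, with the arm means constrained equal at baseline.

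Align the Outcomes and analysis sections so that both name the same quantity, for example the between-arm difference in mean home SBP at 12 months, adjusted for baseline. For consistency with the revised model, baseline SBP should then also be among the imputation predictors; this follows from the change and is not a separate finding.

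The cost is wording only, best settled before outcome data are examined by arm. The sample size stays as it is. The outcome definition already implies a baseline home SBP, but the data-collection section says only that blood pressures are recorded at baseline according to guidelines. The text should therefore state which baseline home series supplies the value.

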## Methods

### Study Objectives

The primary aim of this study is to assess the mean difference in SBP at 12 months, from baseline in remote communities in Northern Alberta through a pragmatic RCT, comparing HBPT + usual care versus HBPT + a case manager. Secondary aims of the study will include:

Proportion of patients who maintained home SBP within guideline target (<130 mmHg)^10,11^ from baseline to the end of the study.Proportion of patients who remained within guideline target SBP (<130 mmHg),^10,11^ throughout the study.The user acceptability of HBPT for BP control, using a qualitative approach.The cost-effectiveness and cost utility of HBPT combined with a protocol-based case management approach among remote-dwellers with CKD compared to the usual care.5.Proportion of adverse events, eg, syncope, hypotension requiring assistance or medical attention, worsening of kidney function (2x serum creatinine or 50% decline in estimated glomerular filtration rate [eGFR]), and/or electrolyte abnormalities [hyperkalemia ≥ 6.5 mmol/L], in each arm of the study.

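### Robust-variance Poisson regression is fixed for adverse outcomes, and gives a spuriously tiny P value whenever a separately tested event type has no events in one arm

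*Protocol article*

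**What the plan says.** In the Protocol article, Plan for Data and Statistical Analysis, one method covers every binary outcome: "For the dichotomous outcomes (patients who maintained the SBP guideline and adverse outcomes), we will use Poisson regression with robust error variance". Its stated purpose is to test the intervention effect. The same section adds "We will adjust for eGFR for all the analyses" and "All estimated effect sizes will be reported along with 95% confidence intervals, and P<0.05 was considered statistically significant". It makes no exception for sparse or empty cells.

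Adverse events are a named secondary aim under Study Objectives: "Proportion of adverse events, eg, syncope, hypotension requiring assistance or medical attention". That list goes on to worsening kidney function (doubled creatinine or a 50% fall in eGFR) and potassium of at least 6.5 mmol/L. Outcomes lists adverse events again. Neither section says whether each type is compared separately or all are pooled, and no expected event rate is given.

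Arm sizes come from Sample Size Estimation: "the required sample size will be ~58 patients per arm, or 116 in total", then "Accounting for ~20% attrition over 1 year, we will recruit 73 patients per arm, for a total of 146 patients".

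**The concern.** Poisson regression with a sandwich variance is a sound way to estimate a rate ratio for a common binary outcome such as SBP-target attainment, which the article assumes to be 50% in the control arm. The listed adverse events are severe and are counted over one year in 58 to 73 patients per arm, so an arm with no events of a given type is plausible. In that case the Wald test from this model breaks down in the dangerous direction: it reports a vanishing P value rather than a wide interval. A single event could then meet the plan's significance rule, as apparent harm or as apparent safety of case management.

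**Working it through.** **Inputs.** From the article: alpha 0.05 (sidedness not stated; two-sided reproduces the figure), power 0.80, SD 19 mmHg, difference 10 mmHg, about 20% attrition, 1:1 allocation. Assumed, because the article gives none: an event risk of 1 to 10% per type, equal in both arms.

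**The plan's arm sizes reproduce.** n = 2(1.960 + 0.842)² × 19² / 10² = 56.7 by the normal approximation. The t-test gives 57.6, so 58 per arm. Allowing for attrition, 58/0.80 = 72.5, so 73 per arm and 146 in total.

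**Why the standard error stays small.** Take arms of n patients, with e events in one and none in the other, and no covariate. The sandwich variance of the log rate ratio is the sum over arms of Σ(y − μ)²/(nμ)².

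- Arm with events, μ = e/n: [e(1 − e/n)² + (n − e)(e/n)²]/e² = 1/e − 1/n.
- Empty arm, at whatever small μ the iteration stops: nμ²/(nμ)² = 1/n.
- Sum: 1/e, so SE = 1/√e.

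The model-based variance is 1/e + 1/(nμ), which grows without limit as μ falls to 0. That term is the proper warning, and the sandwich removes it. With e = 1 the SE is 1.0, so any stopping value of the log rate ratio beyond ±1.96 gives P<0.05. The fits stop near ±20.

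**Fitted tables, 58 per arm, no covariate** (software SEs are within rounding of 1/√e)

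| Events | Robust SE | Robust P | Model-based P | Fisher P |
|---|---|---|---|---|
| 1 v 0 | 0.99 | 6e-94 | 0.999 | 1.00 |
| 2 v 0 | 0.70 | 3e-189 | 0.999 | 0.50 |
| 3 v 0 | 0.56 | about 0 | 0.999 | 0.24 |

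With an eGFR-like covariate, P stayed below 1e-48 in every table tried at 58 and 73 per arm, in either direction. The size of the exponent is an artefact of where iteration stops, but significance is not: an adjusted 1 v 0 fit cut off after 5 iterations still gave P=0.0002.

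**How often one arm is empty.** With z = (1 − p)ⁿ, the probability that exactly one arm has no events is 2z(1 − z). For p = 2% and n = 58, z = 0.98⁵⁸ = 0.310 and 2 × 0.310 × 0.690 = 0.428. The false-positive rates below are from simulated null trials with an eGFR-like covariate. Repeated runs varied by about 3 percentage points or less around them.

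| Assumed risk per type | One arm empty, n=58 | False positive, n=58 | One arm empty, n=73 | False positive, n=73 |
|---|---|---|---|---|
| 1% | 49% | 49% | 50% | 49% |
| 2% | 43% | 43% | 35% | 35% |
| 3% | 28% | 28% | 19% | 20% |
| 5% | 10% | 9% | 5% | 5% |
| 10% | 0.4% | 3% | 0.1% | 4% |

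In the 4,000-trial runs at least 99.7% of trials with one empty arm were declared significant. Trials with events in both arms added at most 3.2 percentage points. The failure is therefore specific to an empty arm.

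**Pooled reading.** With four independent types at risk p each, the any-event risk is 1 − (1 − p)⁴ and z = (1 − p)⁴ⁿ.

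- p = 1%: any-event risk 3.9%; one arm empty in 18% (n=58) or 10% (n=73).
- p = 2%: any-event risk 7.8%; 1.8% or 0.5%.
- p = 3%: any-event risk 11.5%; 0.2% or less.

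**The case against.** The strongest reply is that an article names a general method and leaves the empty-cell contingency to the analysis plan, which is not shown. That would answer a complaint about a missing fallback. Here, though, the article itself assigns the method to adverse outcomes and sets the significance rule, and that stated rule is what misfires.

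Three other objections stand and limit the point.

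- **Rarity is not documented.** A reader might infer that these events are rare. No rate is given, and in patients with CKD whose antihypertensive treatment is titrated, hypotension needing assistance may not be rare. The figures hold only across the assumed range.
- **The unit of analysis is open.** The aim can be read as one pooled outcome with the event types as examples. On that reading the problem is small unless each type is near 1%.
- **The arm size matters.** With all 73 randomised patients analysed, as intention to treat implies, the excess has gone at 5% risk.

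A reader might also infer that a false result would pass into the report unnoticed. The documents do not support that. Outcome variables are also to be described by counts and proportions, and a log rate ratio of 20 is a rate ratio in the hundreds of millions. A careful analyst may well stop there, but the article does not say what to do next, and a test chosen after seeing the counts is no longer pre-specified. The planned software, Stata, was not run. The sandwich algebra is the same, though the stopping value may differ.

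**Conclusion.** The concern holds in conditional form. If event types are tested separately and one arm has none, the method as written makes even 1 v 0 significant. At assumed risks of 1 to 3% per type, the chance of a false positive for a given type is roughly 20 to 50%, against the nominal 5%. At 5% risk it is about 9% with 58 per arm and at its nominal level with 73; at 10% there is no excess. The primary outcome and the SBP-target outcomes are unaffected. The documents do not support the stronger reading that the safety comparison is invalid whatever the event rates and however the events are grouped.

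**What to change.** Keep robust Poisson regression for the SBP-target outcomes. For each adverse-event type, pre-specify the number of patients with the event by arm, a risk difference with an exact or score confidence interval, and an exact test (Fisher or mid-P) as the reported comparison. State that no robust Wald P value is reported when an arm has no events. The eGFR-adjusted model can be kept for a pooled any-event outcome that has events in both arms; say whether such an outcome is intended.

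The cost is analysis wording only: no patients, visits or data. The downside is that exact tests are conservative and unadjusted for eGFR. Fisher's false-positive rate was at most 1.1% for assumed risks of 0.5 to 5%, and with 58 per arm 5 v 0 gives P=0.057 and 6 v 0 gives P=0.027. The interval for the risk difference should therefore carry most of the interpretation.
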